**Phase 2 Selection of Subjects**

We estimate that approximately 120 Veterans will be consented and screened, with 50 being enrolled and randomized to a study condition, and a final sample of 40 participants who complete all study procedures. However, given that the subsequent full RCT will use intent-to-treat analysis, we will include all 50 participants in descriptive statistics and primary analyses. Study inclusion and exclusion criteria are outlined below.

Phase 2 Inclusion/Exclusion Criteria:

| Subjects must meet **all** inclusion criteria: | Subjects must not have **any** exclusion criteria: |
| --- | --- |
| | - Is a US Veteran - Meets DSM-5 criteria for tobacco use disorder - Is between the ages of 18 and 75 - Smokes an average of 10 cigarettes per day for the past 6 months, with carbon monoxide (CO) level > 6 ppm - Is willing to attempt smoking cessation - Meets DSM-5 criteria for current PTSD diagnosis - Speaks, reads and writes English - Is willing to sign a Duke consent for those portions of the study that occur at Duke - Has been stable on psychotropic medications for at least three months | | --- | | - Has had a substance use disorder other than tobacco in the preceding 3 months - Has a history of myocardial infarction in the past 6 months or has another contraindication to NRT - Has a contraindication to TMS or MRI   - Personal or family history of a seizures or epilepsy   - History of neurological condition that increases the risk of seizures including stroke or transient ischemic attack, cerebral aneurysm, or severe traumatic brain injury from a penetrating head injury, loss of consciousness > 20 minutes at time of traumatic injury, requiring an anticonvulsant medication for seizures, and/or found to have encephalomalacia on baseline MRI   - Structural brain lesion, or prior brain surgery   - Ferromagnetic metal in head (including shrapnel)   - Implanted devices that may be affected by MRI or TMS (pacemaker, medication pump, cochlear implant, implanted deep brain stimulator)   - Is pregnant (to be determined at Duke) - Is unable to complete study procedures - Is currently prescribed bupropion and/or varenicline - Uses other forms of nicotine such as cigars, pipes, chewing tobacco, or vaping - Is unable to provide informed consent due to a major neurocognitive disorder or other reason - Meets criteria for a primary psychotic disorder or current manic episode - Is currently imprisoned or psychiatrically hospitalized - Has previously received rTMS |

**Phase 1 and Phase 2 Subject Recruitment**

Based on group’s previous study that had 14 subjects per group (Addicott et al, 2019) and a meta-analysis of online rTMS studies published by mentor, [name], demonstrating an average sample size of 11 in similar studies (Beynel et al, 2019), we plan to have 14 subjects complete all the procedures in the proposed feasibility study. Based on [name] previous research in the study population (Carpenter et al, 2015), we anticipate a similar attrition rate of approximately 20%. Therefore, we expect to enroll 18 subjects in order to have 14 complete the majority of study procedures. In order to enroll 18 eligible study participants, we estimate that we will need to consent and screen approximately 26 potential participants. The Durham VA Medical Center (DVAMC) will be the recruitment site from which Veterans will be identified. Participants will be recruited primarily from among outpatients at the DVAHCS PTSD clinic, Operation Enduring Freedom/Operation Iraqi Freedom/Operation New Dawn (OEF/OIF/OND) clinic, Women’s Health clinic, and Mental Health clinic, as well as IRB-approved letters inviting people to participate in the study. As further detailed below, we will use proactive recruitment methods to identity (via VA computerized medical records), contact (via introductory letter, toll free opt-out telephone number, and telephone calls), to recruit and consent eligible Veterans. These proactive methods are associated with much higher recruitment rates than those seen in efficacy trials that most typically rely on a reactive recruitment approach (Velicer et al, 2006). In addition, [name] will refer subjects who either screen out or who have not achieved smoking abstinence at the end of their participation in his study. In addition, the Traumatic Stress and Health Research Laboratory has a contact database (see IRB #1080), which contains the contact information of participants in previous studies who have indicated (in writing) a desire to be contacted about other research projects in our lab. Any participant who has expressed interest in learning about participating in studies in our lab will be contacted by phone to ask about participation.

We will use VA Data Access Request Tracker (DART) requests to identify additional Veterans with PTSD and tobacco use disorders. We have used similar procedures to successfully recruit Veterans with PTSD in the past. Any potential participant who is identified via a DART request will be sent a recruitment letter and/or an encrypted email (using Azure) that provides basic information about the study. The letter will inform Veterans that they will be contacted by phone in the coming days regarding their interest in participating in the study. In the letter or email, potential participants will be given an “opt-out” number to call in order to decline participation and/or further contact regarding participation. One to two weeks after the mailing, Veterans who have not called to decline participation will be called by a study staff member to request their participation in the research study.

**Phase 1 and Phase 2 Consent Process**

If any participant contacts or is contacted by the study coordinator regarding participation, a telephone script will be used to inform them about the study and do a preliminary determination of eligibility. If after the telephone screening a participant is considered potentially eligible for participation, he/she/they will be sent the study ICF and HIPAA authorization via DocSign, and will be scheduled for a review of the consent documents by phone or video. They will be asked to mail the documents to the study coordinator and will be scheduled for an initial screening session upon receipt. Participants will also be given a copy of the signed informed consent form and phone numbers to call if they have additional questions about the consent form or the research, if they have any problems during the study, or if they have questions about participating in research studies in general. No study procedures will begin until informed consent has been obtained.

**Phase 1 and Phase 2 Study Interventions**

Smoking Cessation Counseling: [name] laboratory will provide trained therapists to administer five weekly evidence-based smoking cessation counseling sessions. Cognitive behavioral therapy (CBT) for smoking cessation will be provided by a therapist who has been trained in CBT administration. All therapists are rigorously trained and receive ongoing supervision. The counseling sessions will be done via video or telephone.

Smoking Cessation Pharmacotherapy: All eligible participants will be prescribed NRT of at least one nicotine rescue method (e.g., patch, gum, inhaler) at the medical screening evaluation and continued as needed during the duration of the study. NRT will be prescribed by the study physician and mentor, [name]., Ph.D. [name] will write the prescriptions and work with participants' primary care physician or psychiatrist to discuss any contraindications. The applicant, [name]., will serve as a back-up prescriber in the event of [name] absence. If no contact from the primary care physician can be made, the participants' health information will be evaluated by the study physician, who will determine medical clearance to participate in the trial. Neither varenicline nor bupropion will be prescribed due to the potential for increased risk of seizures during rTMS (FDA, 2015; Little and Ebbert, 2016).

Because the study procedures are not targeting PTSD symptoms, participants will be informed during the informed consent process that they will not be asked to stop any ongoing PTSD treatments, nor will they be asked to refrain from beginning new treatments.

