**Phase 1 Study Procedures**

Screening Visit: During the COVID-19 pandemic, participants will provide informed consent and HIPAA authorization via mail via DocuSign where available. Subjects will be screened for safety issues by completing the TMS Adult Safety Screen (TASS; Keel et al, 2001), the Duke MRI Safety Screening form, and the Ohio State University (OSU) TBI Identification Method-Short Form. Subjects will also complete self-report measures and receive a clinician-administered psychiatric interview (see Table 1). Study inclusion and exclusion criteria will be used to determine eligibility. If eligible, the rest of the study visits will be scheduled based on availability of the participant as well as Duke procedures (fMRI scanner, rTMS device).

Medical Screening: Medical clearance for subjects to be enrolled will be made by study physician and mentor, [name]., Ph.D., and applicant, [name]., using the study eligibility criteria, as well as negative results on the TMS Adult Safety Screen (TASS), MRI Safety and OSU TBI screening forms.

Biochemical Verification of Abstinence: Participants will provide exhaled breath carbon monoxide (CO) levels at baseline, the quit date and the 2-week follow-up. Breath CO levels are an effective method for monitoring for cessation, and it has an additional positive impact on shaping and inducing smoking abstinence in the first week of a quit attempt (Benowitz, Hukkanen et al, 2009). If participating remotely, participants will be provided with CO monitors to use at these time points and will perform the CO reading during a telehealth visit in which they can show the results via video; otherwise, this will be performed in-person at a VA facility. We will use a standardized cutoff value of  6 ppm (Beckham et al, 2018). This cut-off value has previously been identified as optimal (Woodward & Tunstall-Pedoe, 1992), with good sensitivity and specificity among outpatients (Middleton & Morice, 2000).

Exploratory smoking outcomes will include point prevalence abstinence based on subject self-report and confirmed using remote-monitored exhaled CO level at the quit date and the 2-week follow-up assessment. Additional measures will be daily number of cigarettes smoked, subjective levels of withdrawal, craving, and smoking urges.

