| | - Is a US Veteran - Is between the ages of 18 and 75 (see Rossi et al., 2021) - Smokes an average of 10 cigarettes per day for the past 6 months, with carbon monoxide (CO) level > 6 ppm - Is willing to attempt smoking cessation - Meets DSM-5 criteria for current PTSD diagnosis - Speaks, reads and writes English - Currently an outpatient at DVAHCS - Is willing and able to participate in rTMS intervention, MRI and all required study visits - Is willing to sign a Duke consent for those portions of the study that occur at Duke. | | --- | | - Has previously received TMS - Has a current substance use disorder other than tobacco - Has a contraindication to TMS or MRI   - Personal or family history of a seizures or epilepsy   - History of neurological condition that increases the risk of seizures including stroke or transient ischemic attack, cerebral aneurysm, or severe traumatic brain injury from a penetrating head injury, loss of consciousness > 20 minutes at time of traumatic injury, requiring an anticonvulsant medication for seizures, and/or found to have encephalomalacia on baseline MRI   - Structural brain lesion, or prior brain surgery   - Ferromagnetic metal in head (including shrapnel)   - Implanted devices that may be affected by MRI or TMS (pacemaker, medication pump, cochlear implant, implanted deep brain stimulator)   - Is pregnant (to be determined at Duke) - Is unable to complete study procedures |

**Phase 2 Research Design and Methods**: The proposed study is a two-arm, parallel design, double-blinded, sham-controlled, randomized trial comparing active- vs sham- rTMS neuronavigated to a region on the post-central gyrus functionally connected to the insula in addition to evidence-based CBT for smoking cessation and NRT.

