**Phase 2 Study Procedures**

Screening Visit: These study procedures are similar to Phase 1 of the project. Once considered eligible to participate in the study, participants will be randomized 1:1 to receive either active rTMS or sham rTMS. Participants will remain blinded to study condition throughout the study. [name] and [name] will also remain blinded to study condition.

Medical Screening: These study procedures are similar to Phase 1 of the project. However, in lieu of one screening session, we will divide the screen tasks between two visits. Diagnostic interviews will be completed at the first visit, and questionnaires and CO readings will be completed at the second.

Biochemical Verification of Abstinence: Participants will provide exhaled breath carbon monoxide (CO) levels at baseline, quit date, end-of-treatment, and at 3-month follow-up visit. We will use a standardized cutoff value of < 5 ppm. In addition, at the post-treatment and 3-month follow-up visit, urinary cotinine will also be collected for more comprehensive bioverification for those participants who are no longer using NRT. Urine samples collected will be sent to LabCorp for analysis.

DUMC Study Procedures: MRI procedures are identical to Phase 1 MRI procedures. MagVenture’s MagPro X100 will be used for rTMS procedures. rTMS parameters will be updated from Phase 1 to Phase 2 due to advances in the field and Phase 1 data. Phase 1 will be 5 daily rTMS sessions of 1 Hz 960 pulses for 16 minutes each. Phase 2 will be 5 days of rTMS treatments twice daily using patterned rTMS, intermittent theta burst stimulation (iTBS; 3-pulse 50-Hz bursts at 5-Hz for 2-s trains, with trains every 10 s) 1800 pulses at 90% rMT for 9 minutes each separated by at least 50 minutes. Active- or sham-rTMS will be determined by utilizing a subject-specific code recognized by the TMS device as active or sham, which then instructs staff as to which side of the TMS coil to use. The Magventure B65 A/P coil has identical sides, but the computer will know which side to use based on each participant code. A cue provocation procedure to induce nicotine cravings will be conducted prior to rTMS treatments using a video of smoking-related images as well as instructions for handling of a cigarette and lighter. Following the last rTMS session, a second fMRI scan (post-rTMS fMRI) will be conducted at least 1 hour and up to 24 hours later.

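### The Phase 1 exclusions, unlike those of Phase 2, do not name current bupropion or varenicline use, a seizure hazard during rTMS that the protocol itself names

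*Protocol*

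**What the plan says.** Under Phase 1 and Phase 2 Study Interventions, the paragraph on pharmacotherapy reads "Neither varenicline nor bupropion will be prescribed due to the potential for increased risk of seizures during rTMS". The section heading covers both phases, and the reason given is rTMS in general, not one stimulation pattern. The same paragraph has the study prescriber "work with participants' primary care physician or psychiatrist to discuss any contraindications". If that outside clinician cannot be reached, the study physician reviews the health information and decides on clearance for the trial. The next paragraph says that participants need not stop PTSD treatments under way and may begin new ones.

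The two exclusion lists differ. In Phase 2 Selection of Subjects the list contains "Is currently prescribed bupropion and/or varenicline - Uses other forms of nicotine such as cigars". In Phase 1 Selection of Subjects the nearest entry is the general one in "Has a current substance use disorder other than tobacco - Has a contraindication to TMS or MRI". Its sub-items cover seizure history, neurological conditions, brain lesions or surgery, metal, implants and pregnancy. The only medicine mentioned there is an anticonvulsant, as a marker of severe brain injury.

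On how eligibility is decided, Phase 1 Study Procedures says "Study inclusion and exclusion criteria will be used to determine eligibility". Medical clearance is then made "using the study eligibility criteria, as well as negative results on the TMS Adult Safety Screen (TASS") and negative MRI-safety and brain-injury forms.

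**The concern.** The protocol names a hazard, gives rTMS as the setting in which it arises, and acts on it only through the study's own prescribing. A participant who brings the drug along from another prescriber faces the same named hazard. Phase 2 has a written entry rule for that person and Phase 1 does not. Because Phase 1 clearance is tied to the listed criteria plus the screening forms, a drug that the list does not name is left to a general item, a form whose content is not shown, or case-by-case judgement. What is at stake is the safety of individual Phase 1 participants and consistent handling of the same hazard across phases. The feasibility endpoints and planned numbers are not affected.

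**Working it through.** The protocol states no figure to reproduce, so the check compares the text of the two phases.

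| Element | Phase 1 | Phase 2 |
| --- | --- | --- |
| Study will not prescribe either drug, on seizure grounds | Yes (shared section) | Yes (same section) |
| Current prescription of either drug is an exclusion | No | Yes |
| General TMS/MRI contraindication item | Yes, 6 sub-items | Yes, the same 6 sub-items |
| Screening and medical clearance | Listed criteria plus negative safety forms | Described as similar to Phase 1, split over two visits |
| Discussion with the outside clinician, fallback to study physician | Yes (shared section) | Yes (same section) |

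**Step 1: count the exclusion lines.**
- Phase 1: 4 main items + 6 sub-items = 10 lines, of which 0 name either drug.
- Phase 2: 10 main items + 6 sub-items = 16 lines, of which 1 names them.

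These counts confirm only that the Phase 1 line is absent. They do not measure risk.

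**Step 2: ask whether the non-prescription rule covers a current user.** It does not. It governs what the study team writes, and a prescription from elsewhere lies outside it.

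**Step 3: ask whether the general safeguards make a named line unnecessary.** Phase 2 has the same contraindication item, similar screening and the same physician review, and its list still names the drugs. So the presence of those safeguards in Phase 1 does not by itself show that a named line is redundant there.

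**Step 4: check whether a difference in stimulation could explain the difference in lists.** Phase 2 Study Procedures gives the Phase 1 dose: "Phase 1 will be 5 daily rTMS sessions of 1 Hz 960 pulses for 16 minutes each". It gives Phase 2 as 1,800 pulses twice daily for 5 days.
- Phase 1: 960 × 5 = 4,800 pulses per participant.
- Phase 2: 1,800 × 2 × 5 = 18,000 pulses per participant.
- Ratio: 18,000 / 4,800 = 3.75.

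The heavier Phase 2 schedule is a possible reason for a stricter list, but the protocol does not give it. The seizure sentence in the shared section draws no distinction between the schedules. The ratio is not a measure of relative seizure risk.

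**Step 5: size.** Expected harm would need the proportion of Phase 1 enrollees on either drug and the seizure probability under this stimulation. The protocol gives neither, so no number can be attached.

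**The case against.** The strongest reply is that nothing here is contradictory. A rule about prescribing and an exclusion list that is silent on two drugs can both stand. The general contraindication item is not said to be exhaustive, and a team that believes these drugs raise seizure risk can apply it to a current user. Clearance lies with the study physician, the same role that prescribes NRT under the seizure sentence, and review by that physician extends to entry into the trial. The TASS items are not shown. All stimulation takes place at Duke, and the risks of those procedures are set out in a separate Duke protocol, also not shown. Any of these may already catch such a person. This stands, and it is why the point is minor.

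It is also fair that the Phase 2 line carries no stated reason. It sits beside the item on other nicotine products, which would fit control of confounding in a sham-controlled comparison of abstinence. Phase 2 adds several other exclusions that Phase 1 lacks, so the lists differ in general and not only on these drugs. That stands too: the safety motive for the Phase 2 line is an inference. But the mismatch between the seizure sentence and the Phase 1 list does not depend on that motive.

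Three stronger readings are tempting and are not supported:

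- A reader might infer that Phase 1 allows current users to be stimulated. The text shows only that no written line names them.
- A reader might infer that the recruitment route brings in such people, since both phases take referrals of those "who either screen out or who have not achieved smoking abstinence at the end of their participation in his study". The protocol does not say what those people take.
- A reader might infer that the permission to continue or start PTSD treatments admits these drugs. The protocol does not class either drug as a PTSD treatment.

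**Conclusion.** The point holds as a low-severity patient-safety clarification. For a hazard that the protocol names for both phases, Phase 2 has an explicit entry rule, while Phase 1 relies on a general item, a form and judgement. It rests on two readings: that the non-prescription sentence applies to Phase 1, as its heading says, and that it covers study prescribing only, as its wording says. It would fall away if the TASS or the Duke protocol already excludes current users. No endpoint, sample size or error rate is affected, and the size of the risk is unknown.

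Whether the criterion can still be changed is uncertain. Phase 2 Study Procedures attributes the new stimulation settings partly to data from Phase 1, which suggests that Phase 1 is finished or well advanced, yet it also describes Phase 1 in the future tense.

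**What to change.** If Phase 1 is still enrolling, add the Phase 2 exclusion for a current prescription of bupropion, varenicline or both to the Phase 1 list. The cost is one line of text and slightly slower recruitment.

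If Phase 1 is closed, no criterion can change. In that case, report how many Phase 1 participants were on either drug at entry, next to the TMS side-effect results, but only if the medical record allows it. Table 1 lists no concomitant-medication form, so the availability and cost of that count cannot be assumed. It is a reporting suggestion and repairs nothing in the design.

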**Phase 1 and 2 Costs and/or Payments to Subjects**

Phase 1: Subjects will receive payments ($100/session) for all assessment procedures completed including baseline screening and two follow-up assessments. We will also pay participants $100 each for receipt of their DUMC study data at VA. This reimbursement strategy is consistent with our prior work (CSR&D Merit CX001486). Subjects will receive a total of $500 if all procedures are completed and data are received, Participants will receive free smoking cessation counseling and a 5-day course of rTMS treatment. Participants will receive NRT via a telehealth clinic and may be charged co-pays as indicated by their eligibility status.

Phase 2: Participants will be paid $100 each of the following visits: screening, quit date, end of treatment, and 3-month follow-up. Participants will also be paid a total of $200 each for receipt of their Duke fMRI data at VA. Participants can receive up to a total of $600 for phase 2 of the study.

